#### Socioeconomic transplant derailers

Multiple characteristics also are thought to be associated with having greater levels of socioeconomic stressors that may impact successful completion of transplant evaluation. These include patients’ education level, the type of health insurance they have (private, government, multiple sources, no insurance), and their employment status (full time, part time, disability, other financial assistance programs, no employment). Additional measures such as income vulnerability (e.g., “If your family lost your current income, how long could you continue to live in your current situation?”) [51], family obligations, access to transportation [52], and feelings of safety in their neighborhood will also be assessed to determine the level of vulnerability each patient faces. Lastly, patients will be asked a series of two open-ended questions to determine: 1) how personal life factors might make it difficult to get a transplant (“What are you dealing with that might get in the way of you pursuing transplant?”) and 2) what plans the patient already has in place to overcome the identified barrier (“Do you have any ideas about how you could make sure that this doesn’t stop you from pursuing transplant?”).

#### Social support and availability of living donors

Social support will be assessed by examining discordance on responses to two items measured on a 4-point Likert scale ranging from “None” to “A great deal”: “In the past 6 months, how much help or support have you received, related to your kidney disease?”; “In the past 6 months, how much help or support have you needed, related to your kidney disease?” [52]. Availability of donors will be assessed by measuring the number of close and extended family members and friends a patient has, presence of kidney disease or other comorbidities (e.g., diabetes and hypertension) in these groups, and the number of donor offers.

#### Transplant education and health literacy

Patients’ previous transplant education will be evaluated with four “Yes/No” questions that explore whether they have: 1) read brochures, 2) watched videos, 3) browsed the internet, and 4) talked to doctors or medical staff about LDKT or DDKT. Patients responding “Yes” to any of the items will then be asked how much time they have spent learning about transplant through that distinct method. Subjective health literacy and numeracy [53] will be assessed with two items scored on Likert-type scales: “How often do you have someone (like a family member, friend, hospital/clinic worker or caregiver) help you read hospital materials?”, “How confident are you filling out forms by yourself?”

#### Evaluation and process measures

At the 8 month assessment, or if patients receive a transplant or are deemed permanently ineligible for transplant before then, patients will be asked to assess the cultural competence of their healthcare providers during the evaluation process (e.g., “How often were you treated unfairly at the transplant center because of your race or ethnicity?”) on a 4-point scale ranging from “Never” to “Always”. Cultural competence will be further explored with 4 items that assess how much patients agreed that they felt trust and concern from their providers (e.g., “Did you feel you could trust them with your medical care?”; “Did you feel they really cared about you as a person?”). All cultural competence measures were adapted from the Consumer Assessment of Healthcare and Provider Systems (CAHPS) Clinician & Group Survey [54].

Patients will also be asked a series of questions about their informed decision making. The decisional conflict scale [55] was adapted to reflect three kidney disease treatment options including remaining on dialysis, getting a DDKT, and taking actions to pursue LDKT. After identifying which treatment option(s) they have chosen, patients will be asked to evaluate their decision (e.g., “I know the risks and side effects of each option”; “I am choosing without pressure from others”; “I am satisfied with my decision”) using a 5-point, Likert-type scale ranging from “Strongly Agree” to “Strongly Disagree”. To assess whether a patient has made an informed decision, patients will respond using a 4-point Likert-type scale ranging from “Completely Disagree” to “Completely Agree” to the following questions: “I have all the facts I need to make an informed decision about whether or not to pursue deceased donation” and “I have all the facts I need to make an informed decision about whether or not to pursue LDKT”.

### Data management and statistical considerations

To ensure confidentiality and security of patients, all data, including de-identified audio-recordings of patient interviews, will be stored in university-maintained, encrypted, password protected servers. Also, in accordance with NIH policy, we have established a data safety and monitoring board to monitor our trial’s progress. All study data will be captured in two electronic databases. First, registration data, patient demographics, patient tracking fields, and transplant status/medical records will be captured in a REDCap patient registration system [46]. Study personnel can check on patients’ records by examining their data entry form or through reports generated in REDCap. The records of patients who refuse to participate or are never successfully recruited to the study will be retained in the REDCap registration database and de-identified at the end of the study so that patterns in recruitment can be analyzed and reported.

Second, assessments of transplant decision-making, factors that could derail patients in their pursuit of transplant, health literacy, medical mistrust, and social support at baseline, 4 and 8 months post-baseline and relevant coaching recommendations will be captured in the YPT computerized survey and coaching program. The YPT system has been programmed using Pro-Change Behavior Systems, Inc.’s proprietary behavior change software that utilizes spreadsheets, within which statistical decision rules for generating patient feedback, assessment questions and response options, and multimedia specifications are programmed and configured. An offline Java process converts the information on these project configuration spreadsheets into Java objects, and stores the Java objects in a single serialized file. Then TTMX, a Java application, accesses the rules defined in the serialized file to give TTM-based, individualized feedback. As a participant proceeds through the program, TTMX compiles the text and graphic components of each screen based on the participant’s responses and on what have been programmed in the spreadsheets. The statistical decision rules are derived from multivariate analyses. An integrated back-end database allows for dynamic stored responses which enables dynamic tailoring. The integrated database allows for a fully-integrated user experience regardless of their chosen method of engagement (i.e., coaches, online, and others).

### Power and sample size

The sample size and power calculation for this trial was treated as a test of the proportional differences between YPT and UC patients in the Action stage of LDKT readiness at 8-months post-baseline. Based on previous work, we conservatively estimated that, at 8 months post-baseline, 10% of UC patients and 20% of patients in YPT group would reach the Action stage [10, 33]. Assuming a one-tailed alpha of 0.05, a sample size of 300 patients per group is required at 8 months post-baseline to achieve power of 0.80 (total n = 600). Assuming an 8-month post-baseline retention rate of 66%, a total sample size of 450 per education condition will need to be recruited/consented at baseline (n = 900). This sample size will provide sufficient sensitivity to detect a difference in increase in LDKT readiness (i.e., moving to Action) of about 10% between treatment (YPT) and control (UC) groups using logistic regression.

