### RCT overview

In this study, we will conduct an educational intervention as Black, Hispanic, and White ESRD patients present for and undergo transplant evaluation, and take actions to pursue DDKT and LDKT. This longitudinal, parallel RCT has two treatment conditions with equal allocation, the YPT Intervention and the UC control education conditions (Figure 2). Patients in both groups will be surveyed prior to presenting at the transplant center (baseline), and at 4- and 8-months post-baseline. Patients in the intervention group will also be surveyed an additional time during their in-person transplant evaluation meeting. Completion of transplant evaluation and receipt of LDKT will be assessed for both groups using medical records 18-months post-baseline.

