### Statistical analyses

All statistical tests will employ an intent-to-treat (ITT) approach wherein subjects will maintain their assignment to the treatment condition to which they were originally randomized regardless of whether they actually end-up receiving the planned interventions or not [56]. Multiple imputation of missing data will be used for the analyses [57]. The alpha level for all tests will be set at 0.05, and random effects models will be used to account for longitudinal measurement and linear regression employed for normally distributed outcomes, logistic regression for binomially distributed outcomes, and Poisson regression for count outcomes. The social, demographic, and other characteristics of patients who refuse to join the study or are never successfully contacted will be compared to those who do not to determine if the patient selection procedure has resulted in a biased sample. A similar analysis will be conducted to compare the patients who drop-out of the study to those who do not to determine if patient attrition has biased the sample.

To test whether, compared to the UC education condition, Black, Hispanic, and White patients receiving YPT increase in their LDKT readiness, we will first examine the proportion of individuals moving into the Action stage for readiness to accept a LDKT 8 months post-baseline between the YPT and UC conditions. For a more fine grained assessment of change in LDKT and DDKT readiness throughout the study, change by three occasions (baseline, 4 months post-baseline, and 8 months post-baseline) will be examined. To assess differences in transplant knowledge, DDKT/LDKT self-efficacy, and DDKT/LDKT decisional balance, comparisons between the YPT and UC conditions by these three occasions will be made to determine if the intervention increases transplant knowledge, DDKT/LDKT self-efficacy, and DDKT/LDKT decisional balance scales. Finally, differences in the number of small steps toward LDKT and DDKT will be examined at these three time points.

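### The stated 300 per group does not follow from the plan's own inputs: 10% versus 20% at one-tailed alpha 0.05 needs about 157 per group for 80% power, and 300 gives about 96%

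*Protocol article*

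**What the plan says.** The section Power and sample size of the protocol article gives a full set of inputs and one result.

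- **Test:** the calculation was "treated as a test of the proportional differences between YPT and UC patients in the Action stage of LDKT readiness at 8-months post-baseline".
- **Rates:** "10% of UC patients and 20% of patients in YPT group would reach the Action stage".
- **Error rate:** "Assuming a one-tailed alpha of 0.05".
- **Result:** "a sample size of 300 patients per group is required at 8 months post-baseline to achieve power of 0.80", that is, 600 in total.

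The section RCT overview confirms 1:1 randomisation: "two treatment conditions with equal allocation". The 300 per group is the number left at 8 months. It is then raised to 450 per group (900 in total) for 66% retention.

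The section Statistical analyses adds "The alpha level for all tests will be set at 0.05" and does not say whether tests are one- or two-sided.

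**The concern.** The paragraph states everything needed to repeat the calculation, and the repeat gives about half the stated number. So at least one of the rates, the power or the sample size is misreported, or 300 was chosen for a reason that is not given.

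This is the only sample-size justification in the article, and the target of 900 patients rests on it. Anyone using it to judge slow recruitment or heavy attrition would be misled. As written, it implies that power falls below 80% once fewer than 300 per group remain. On its own assumptions, 80% power needs only 157 of the 450 recruited per group (157/450 = 35%).

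**Working it through.** **Inputs** (Power and sample size; allocation from RCT overview): p1 = 0.10, p2 = 0.20, difference d = 0.10, mean rate 0.15, one-tailed alpha 0.05 (z = 1.645), power 0.80 (z = 0.8416), allocation 1:1.

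**Step 1. Try to reproduce the stated 300.** With the pooled variance under the null:

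n = [z_alpha × √(2 × 0.15 × 0.85) + z_power × √(0.10 × 0.90 + 0.20 × 0.80)]² / d²

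- One-tailed: [1.645 × 0.505 + 0.8416 × 0.500]² / 0.01 = (0.831 + 0.421)² / 0.01 ≈ 156.6, so **157 per group** (314 in total).
- Two-sided (z = 1.960): (0.990 + 0.421)² / 0.01 ≈ 199.0, so **199 per group**.

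The stated figure is not reproduced: 300/157 = 1.9.

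**Step 2. Check whether another standard method gives 300.** Required number per group for 80% power at 10% versus 20%:

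| Method | One-tailed 0.05 | Two-sided 0.05 |
|---|---|---|
| Pooled variance | 157 | 199 |
| Unpooled variance | 155 | 197 |
| Arcsine | 154 | 195 |
| Wald test of log odds ratio (logistic regression) | 164 | 208 |
| Continuity-corrected | 177 | 219 |
| Fisher's exact test | about 175 | not solved for |

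The largest entry is 219.

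**Step 3. Power at 300 per group.**

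- Standard error under the null: √(0.255/300) = 0.02915. Under the alternative: √(0.25/300) = 0.02887.
- One-tailed: (0.10 − 1.645 × 0.02915)/0.02887 = 1.80, so power = **0.964**.
- Two-sided: (0.10 − 1.960 × 0.02915)/0.02887 = 1.48, so power = **0.931**.

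Other methods at 300 per group:

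| Method | One-tailed | Two-sided |
|---|---|---|
| Wald test of log odds ratio | 0.958 | 0.921 |
| Continuity-corrected | 0.954 | 0.915 |
| Fisher's exact test | 0.957 | 0.920 |

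All are well above 0.80.

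**Step 4. Check the attrition step.** 300/0.66 = 455 and 300/0.67 = 448, so 450 recruited per group fits 300 at 8 months. Attrition does not explain the gap, because 300 is already the number after attrition. Starting from 157, the same step gives 157/0.66 = 238 per group.

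**Step 5. Look for another stated driver.** Power and sample size mentions no clustering, multiplicity adjustment or power within racial groups. Statistical analyses plans race interactions and repeated-measures comparisons, but does not tie the sample size to any of them.

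**The case against.** The strongest reply is that the error does no harm. On the written rates the main comparison has more power than claimed, even two-sided, and no test or estimate changes. That stands, and it limits the severity. It does not make the sentence true: the article says 300 are required, and they are not.

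A second reply is that an article condenses a fuller protocol. That would excuse an omission. Here the inputs and the result are both printed and they disagree, which a longer document would not cure.

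Three stronger readings are tempting, and the document does not support them.

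- **That the closing sensitivity sentence is also wrong.** It says the sample can detect a "difference in increase in LDKT readiness (i.e., moving to Action) of about 10" per cent between groups. At 300 per group, 80% power is already reached at about 10% versus 16.9% one-tailed (17.9% two-sided), so a reader might call the sentence mistaken. But it claims only that the size is enough for about 10 points, which is true. It does not call this the smallest detectable difference.
- **That 300 came from a control rate of 40–50%, so that true power is much lower.** For 40% versus 50%, 300 per group gives 0.79 one-tailed and 0.69 two-sided. The article states no such rate, and other scenarios fit as well: 20% versus 30% two-sided gives 0.81; 30% versus 40% one-tailed with continuity correction needs exactly 300; and if 300 was meant as a total, 150 per group at 10% versus 20% gives 0.785. Since several incompatible origins fit, none is shown.
- **That the retention figure needs correcting.** 450 × 0.66 = 297, but Patient recruitment, eligibility, randomization, and retention speaks of approximately 33% attrition and approximately 600 patients, and two-thirds of 450 is 300. This is rounding; one-tailed power at 297 is 0.963.

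**Conclusion.** The point holds as a misstated figure. With 10% versus 20%, one-tailed alpha 0.05, 80% power and equal groups, about 157 per group are needed at 8 months (about 177 with continuity correction; 199 to 219 if two-sided), not 300. At 300 per group the power is about 96% one-tailed and 93% two-sided, not 80%.

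This rests only on the inputs the article states and on treating the comparison as one of two independent proportions, as the article does. The choice of test moves the one-tailed requirement between 154 and 177, far short of the gap.

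It should be fixed, but it is not critical. On the stated assumptions the trial is better powered than it says, and the recruitment target need not change. Where 300 came from cannot be settled from the article.

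**What to change.** Keep 450 recruited per arm and restate the paragraph in one of two ways.

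1. If 10% versus 20% is the real assumption: *With about 300 evaluable patients per group, 10% versus 20% is detected with about 96% power at one-tailed alpha 0.05 (93% at two-sided 0.05); 80% power would need about 157 per group.*
2. If 300 came from other rates, another power target or another aim, state those actual inputs in place of the present ones.

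Giving both one-tailed and two-sided power leaves the stated alpha as it is and does not prejudge which will be used. The cost is wording only, with no change to recruitment, follow-up or analysis.

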### Statistical analyses

All statistical tests will employ an intent-to-treat (ITT) approach wherein subjects will maintain their assignment to the treatment condition to which they were originally randomized regardless of whether they actually end-up receiving the planned interventions or not [56]. Multiple imputation of missing data will be used for the analyses [57]. The alpha level for all tests will be set at 0.05, and random effects models will be used to account for longitudinal measurement and linear regression employed for normally distributed outcomes, logistic regression for binomially distributed outcomes, and Poisson regression for count outcomes. The social, demographic, and other characteristics of patients who refuse to join the study or are never successfully contacted will be compared to those who do not to determine if the patient selection procedure has resulted in a biased sample. A similar analysis will be conducted to compare the patients who drop-out of the study to those who do not to determine if patient attrition has biased the sample.

To test whether, compared to the UC education condition, Black, Hispanic, and White patients receiving YPT increase in their LDKT readiness, we will first examine the proportion of individuals moving into the Action stage for readiness to accept a LDKT 8 months post-baseline between the YPT and UC conditions. For a more fine grained assessment of change in LDKT and DDKT readiness throughout the study, change by three occasions (baseline, 4 months post-baseline, and 8 months post-baseline) will be examined. To assess differences in transplant knowledge, DDKT/LDKT self-efficacy, and DDKT/LDKT decisional balance, comparisons between the YPT and UC conditions by these three occasions will be made to determine if the intervention increases transplant knowledge, DDKT/LDKT self-efficacy, and DDKT/LDKT decisional balance scales. Finally, differences in the number of small steps toward LDKT and DDKT will be examined at these three time points.

To determine whether, compared to the UC group, Black, Hispanic and White patients receiving YPT are more likely to complete transplant medical evaluation and pursue LDKT 18-months post-baseline, regression models will be fit with: 1) only the treatment condition as a predictor; 2) race added-in as a covariate; 3) an interaction term between treatment and race. To examine whether the YPT’s effectiveness in changing LDKT decision-making and behavior is different between Blacks, Hispanics and Whites, comparisons will be made of proportional forward movement in readiness at 8 months post-baseline between Black, Hispanic and White patients in the YPT condition. Also, Black, Hispanic and White patients will be compared on three occasions (baseline, 4 months post-baseline, and 8 months post-baseline) to determine if access to YPT increases transplant knowledge differently for Black, Hispanic and White patients through this follow-up period and if the intervention has different effectiveness on the increase in proportion of living donors being evaluated for LDKT and increases in the proportion of LDKTs among Black, Hispanic and White patients 18-months post-baseline.

Finally, to examine how known patient, family, and healthcare system barriers to LDKT act alone and in combination with YPT to affect Black and Hispanic patients’ decision-making and behavior around LDKT, the direct effects of key modifiable and non-modifiable variables known to affect disparities in receipt of LDKT (e.g., medical mistrust, quality of health insurance, physician recommendation to pursue LDKT) on readiness to pursue LDKT, transplant knowledge, completion of transplant evaluation, and receipt of LDKT will be adjusted for in regression models of YPT’s effect on these outcomes for Blacks and Hispanics separately. Then, interactions between YPT and these factors will be added to the models. Specifically, we will model each dependent variable first using the main effects of the barrier variables and of the YPT intervention, and then add two-way interactions between the intervention and the barrier variables. Similar models will be constructed for White patients. Based on these models, we will determine: (1) the estimated magnitude of racial differences between Black, Hispanic and White patients with and without access to the YPT for each outcome, and (2) which patient and care-related variables represent important confounding and modifying effects for explaining racial/ethnic differences in each outcome. These analyses will help elucidate whether the YPT achieves results by attenuating the impact of specific ‘causes’ of racial/ethnic disparities in LDKT.

Qualitative analyses will be performed to understand responses to key open-ended questions asked in the survey, particularly those around socioeconomic barriers to patients’ pursuit of transplant, potential solutions to barriers patients face in their transplant pursuit, and actions patients are willing to take toward LDKT and DDKT. Patients’ responses will be coded and analyzed to determine themes.

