Although the results of this educational intervention were promising, there is evidence that interventions that are individually-tailored to ESRD patients’ needs and preferences may be even more successful at reducing racial disparities in completion of evaluation and receipt of LDKTs [34, 35]. In this manuscript, we describe the protocol of a new randomized controlled trial (RCT) to test the efficacy of a computerized *Your Path to Transplant* (YPT) educational program on decreasing racial disparities in LDKT. The RCT will determine, compared to a usual care education control group (UC) from the transplant center, whether Black, Hispanic, and White patients receiving YPT increase in their readiness to pursue LDKT and transplant knowledge, and whether they become more likely to complete transplant medical evaluation and pursue LDKT. It will also examine whether YPT’s effectiveness in changing LDKT decision-making and behavior is different between Blacks, Hispanics, and Whites. Finally, it will examine how known patient, family, and healthcare system barriers to LDKT act alone and in combination with YPT to affect Black and Hispanic patients’ transplant decision-making and behavior.

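### The trial is sized on a one-tailed 0.05 test, but the analysis rule sets 0.05 for all tests without sidedness or a named primary outcome; a two-sided primary test costs about 3 points of power at the stated rates

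*Protocol article*

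**What the plan says.** Three places in the protocol article bear on this point.

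- **Power and sample size.** The calculation is for the proportion in the Action stage of LDKT readiness at 8 months. It assumes that "10% of UC patients and 20% of patients in YPT group would reach the Action stage". The test is fixed by "Assuming a one-tailed alpha of 0.05". The result is that "a sample size of 300 patients per group is required at 8 months post-baseline", for a power of 0.80.
- **Statistical analyses.** The testing rule is "The alpha level for all tests will be set at 0.05". Sidedness is not given. The section examines movement into the Action stage at 8 months first. It then turns to finer readiness change, knowledge, self-efficacy, decisional balance and small steps, and later to evaluation completion and LDKT at 18 months. No outcome is called primary.
- **Background.** The aims stand side by side: whether those given YPT, compared with usual care, "increase in their readiness to pursue LDKT and transplant knowledge, and whether they become more likely to complete transplant medical evaluation and pursue LDKT".

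**The concern.** The design section and the analysis section do not settle which test will decide whether YPT works. Each way of reading them has a drawback.

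- **One-tailed, as sized.** The probability of declaring benefit when there is none is 0.05. Most readers will assume 0.025, which is what a two-sided 0.05 test gives. A result in the wrong direction, however large, could not be declared significant. The article gives no reason for choosing one tail. The race and barrier interactions listed later have no stated direction, so a one-tailed rule would not fit them.
- **Two-sided.** The power statement then belongs to a test that will not be run.

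Because the sizing outcome is not labelled, the article also does not say which result is confirmatory and which is supportive. What is at stake is the error rate attached to a positive conclusion.

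**Working it through.** **Inputs** (all from Power and sample size, with 1:1 allocation from RCT overview): p1 = 0.10, p2 = 0.20, 300 per group analysed, alpha 0.05, target power 0.80. Normal quantiles: 1.645 (one-sided 0.05), 1.960 (two-sided 0.05), 0.842 (power 0.80).

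**Common terms.** Mean rate = 0.15. Null term A = √(2 × 0.15 × 0.85) = 0.505. Alternative term B = √(0.10 × 0.90 + 0.20 × 0.80) = 0.500. Difference d = 0.10.

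**1. The article's own figure.** n per group = (z_alpha × A + z_power × B)² / d².

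- One-sided: (0.831 + 0.421)² / 0.01 → 157.
- Two-sided: (0.990 + 0.421)² / 0.01 → 199.

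Other standard methods do not reach 300 either:

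| Method | One-sided | Two-sided |
|---|---|---|
| Pooled variance | 157 | 199 |
| Continuity-corrected | 177 | 219 |
| Unpooled | 155 | 197 |
| Arcsine | 154 | 195 |
| Log odds ratio (logistic) | 164 | 208 |

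The stated 300 per group for 0.80 power is therefore not reproduced. It is larger than its inputs require, not smaller.

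**2. Power at 300 per group.** Power = Φ[(d × √n − z_alpha × A) / B], with d × √300 = 1.732.

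- One-sided: Φ[(1.732 − 0.831) / 0.5] = Φ(1.80) = 0.964.
- Two-sided: Φ[(1.732 − 0.990) / 0.5] = Φ(1.48) = 0.931. A simulated Fisher exact test gives 0.914.

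The difference is 3.3 points. At 450 × 0.66 = 297 per group the values are 0.963 and 0.929. Even 90% power two-sided needs only 266 per group.

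**3. How far the small cost depends on the rates.** The same formula with a 10-point difference at other rates (assumptions, not in the article) and 300 per group:

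| Rates | One-sided | Two-sided | Loss (points) |
|---|---|---|---|
| 10% vs 20% (article) | 0.964 | 0.931 | 3.3 |
| 20% vs 30% | 0.883 | 0.809 | 7.4 |
| 40% vs 50% | 0.794 | 0.693 | 10.1 |

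If the stated one-tailed 0.80 were the true power, two-sided power would be about Φ(1.645 + 0.842 − 1.960) = Φ(0.527) = 0.70.

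**4. Several headline questions at 0.05.** Take the four aims in the Background: readiness, knowledge, evaluation completion and LDKT. If there is no effect on any of them and the tests are independent, the chance of at least one false claim of benefit is:

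- all one-tailed: 1 − 0.95⁴ = 18.5%;
- all two-sided, counting only the favourable tail: 1 − 0.975⁴ = 9.6%.

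Positive correlation, which is likely for outcomes on one pathway in the same patients, lowers both.

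**The case against.** The strongest reply is that little is wrong. A one-tailed 0.05 test and a general 0.05 threshold are compatible, the one-tailed choice is disclosed, and the hypotheses are directional. YPT adds education to identical usual care, so the inability to declare harm matters less than it would for a drug. A lead outcome can also be inferred, because the 8-month Action stage drives the sample size and is examined first. Rules on multiplicity are commonly left to a full protocol or SAP, which is not shown.

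Much of this stands. There is no outright contradiction between the two alpha statements, and a missing multiplicity rule is not itself a fault in an article. What remains is that the article states a one-tailed choice without a reason, then fixes a threshold for all tests without saying whether that choice carries over.

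A reader might go further and infer three things that the document does not support.

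- **That success on any one outcome would count as success of YPT.** No such decision rule is written. The analysis section asks separate questions of separate outcomes.
- **That the false-benefit rate is 18.5%.** That figure needs four one-tailed, independent tests. Sidedness is not stated, the two-sided figure is 9.6%, and correlation lowers either.
- **That the 18-month outcomes must be tested in a fixed sequence.** This is one valid scheme among several. The article gives no basis for making LDKT receipt wait on evaluation completion, or for removing knowledge from confirmatory testing.

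It is also fair to object that a two-sided test is cheap only because 300 per group exceeds what the stated inputs need. That objection stands, and the power mismatch has to be disclosed with the recommendation.

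**Conclusion.** The point holds in a limited form. The sidedness of the main test is left open between the power and analysis sections, and the outcome that sizes the trial is not named as primary. Run as sized, the test carries a 0.05 rate of false benefit, twice the conventional 0.025. Run two-sided, it loses 3.3 points of power (0.964 to 0.931) and stays well above the 0.80 target.

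The small cost rests on the article's 10% and 20% and on 300 analysed per group. With higher rates the loss is 7 to 10 points, and at 40% versus 50% two-sided power is 0.69. The statement of 0.80 power at 300 per group does not follow from the stated inputs, and the article does not show which element is off.

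This should be corrected, but it does not undermine the design.

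**What to change.** **In Statistical analyses**, state that tests are two-sided at 0.05, that the proportion in the Action stage of LDKT readiness at 8 months is the single primary outcome, and that all other outcomes are secondary or exploratory. No particular testing order for the 18-month outcomes is needed.

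**In Power and sample size**, replace the one-tailed statement. At 10% versus 20% and 300 per group, two-sided power is about 0.93 (0.96 one-sided), and 0.80 would need about 199 per group (157 one-sided). If other rates were intended when 300 was derived, give them and the power that follows. The recruitment target of 900 can stay.

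**Cost.** The change is to wording, with no added patients, visits or data. Power on the primary outcome falls by about 3 points at the stated rates, and by more if the control rate proves higher. Significant results on the other outcomes, including knowledge, evaluation completion and LDKT receipt, become supportive.
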